***Medical Procedures:***							
Blood Pressure	**√**	**√**	**√**	**√**	**√**	**√**	**√**
Electrocardiogram (ECG)	**√**	**√**	**√**	**√**	**√***	**√**	**√**
Foot Check	-	-	**√**	**√**	**√***	**√**	**√**

***Biochemical measurements:***							
75g-OGTT: Fasting & 120 min glucose	**√**	**√**	**-**	**-**	**-**	**-**	**-**
UE, LFT, Lipid profile, HbA1c%	**√**	**√**	**√**	**√**	**√**	**√**	**√**
Renal function & urine ACR	**√**	**√**	**√**	**√**	**√**	**√**	**√**
TFT	**-**	**-**	**√**	**√**	**√***	**√**	**√**

***Anthropometric measurements:***							
Height	**√**	**√**	**√**	**√**	**√**	**√**	**√**
Weight	**√**	**√**	**√**	**√**	**√**	**√**	**√**
Hip/Waist circumference	**√**	**√**	**√**	**√**	**√***	**√**	**√**
Bioimpedence (% body fat)	**√**	**√**	**√**	**√**	**√***	**√**	**√**
Body Mass Index (BMI)	**√**	**√**	**√**	**√**	**√**	**√**	**√**

***Screening Questionnaires*:***							
Medical/family history/medications	**√**	**√**	**√**	**√**	**√***	**√**	**√**
Alcohol/smoking status	**√**	**√**	**√**	**√**	**√***	**√**	**√**

***Self-reported Questionnaires:***							
Findrisc[45], Cambridge risk scores[46]	**√**	**√**	**√**	**√**	**√***	**√**	**√**
EuroQol, EQ-5D[47]	**√**	**√**	**√**	**√**	**√***	**√**	**√**
WHO-5, BFI 44[48]	**√**	**√**	**√**	**√**	**√***	**√**	**√**
IPAQ[49], Berlin ESS[50]	**√**	**√**	**√**	**√**	**√***	**√**	**√**
Michigan neuropathy[51]	**√**	**√**	**√**	**√**	**√***	**√**	**√**
T2DM: Life Quality/treatment satisfaction	**-**	**-**	**√**	**√**	**√**	**√**	**√**
ADDQoL[52], DTSQ[52], W-BQ 28[52]							

***Arterial measurements sub study:***							
_cf_PWV, PCA[36,37]	**√**	**√**	**√**	**-**	**-**	**-**	**√**

***Biobank storage aliquots:***							
8 × 2 ml Plasma(4), serum (4),	**√**	**√**	**√**	**√**	**√***	**√**	**√**

***Genetic Sample:***							
Whole blood (EDTA)	**√**	**-**	**-**	**-**	**-**	**-**	**-**

Key:

OGTT: 75 g Oral Glucose Tolerance Test (preparation as per WHO expert consensus report -1999)

UE: Biochemistry Urea & Electrolytes panel ACR: Albumin:Creatinine Ratio

LFT: Liver Function Tests (Bilirubin, alanine transaminase, alkaline phosphatase, gamma glutamyl transpeptidase)

HbA1c%: Glycosylated Haemoglobin

Lipid profile: Total, LDL, HDL Cholesterol & Triglycerides

TFT: Thyroid Function Test (Thyroid Stimulating Hormone, free thyroxine T4)

_cf_PWV, PCA: carotid-femoral Pulse wave Velocity Pulse Contour Analysis (Photoplethysmography derived)

Screening Questionnaires*: Completed during Interview with trained research nurse

Anthropometric measurements are performed by trained staff following standard operating procedures, with height being measured to the nearest 0.1 cm using a rigid stadiometer and weight in light indoor clothing measured to the nearest 0.1 kg with a Tanita scale (Tanita, Europe). Body fat percentage is measured via calibrated bio impedance (Tanita, Europe). Body mass index (kgm^-2^) is defined as weight in kilograms divided by height in metres squared. Waist circumference was measured at the mid-point between the lower costal margin and the level of the anterior superior iliac crest to the nearest 0.1 cm.

Brachial blood pressure is measured three times using standardised Omron M7 digital sphygmomanometers (Omron Healthcare, Milton Keynes, UK) with the participant in a seated position. An average of the second and third readings is recorded as per British Hypertension Society guidelines [34] with written instructions for abnormal readings. A 12 Lead electrocardiogram (ECG) is performed using a Nihon Kohden CardioFax Gem machine (Nihon Kohden Europe GmbH, Rosbach vor der Höhe, Germany). An in-house physician interprets ECGs on the day of the visit, codes for ischaemia and left ventricular hypertrophy [35] and reports back to the general practitioner.

Self-completed questionnaires are used to assess baseline smoking status, alcohol consumption, occupation, and ethnicity. Validated questionnaires measuring physical activity, sleep quality, risk of diabetes, neuropathy, and diabetes-specific psychological domains of well being and anxiety are also included (table 1). All measurements are performed by a dedicated team of research nurses trained to document relevant medical information and family history on a standardised case report form during a 20 minute one to one interview on the day of screening. The clinical team are unaware of participants study group allocation or glucose diagnosis.

At major visits (V0-V4, and pre diabetes assessments) further venepuncture is performed for future biomarker research (table 1). Consent is obtained for the -80°C storage of multiple anonymised serum, plasma and whole blood aliquots. These samples contribute to a biobank facilitating translational research exploring the pathogenesis of insulin resistance, vascular complications and genetics of T2DM.

An option for further physiological measurements is incorporated as a sub study amendment at visits V0, V1 and V4. Volunteers consent to return on a separate occasion for non-invasive arterial assessments and blood tests. Trans-cutaneous ultrasonic Pulse Wave Velocity (_cf_PWV), and digital photoplethysmographic pulse contour analysis (PCA) are performed under controlled conditions using commercially available equipment (PT4000, Cardinal Healthcare, Basingstoke, UK) [36,37].

#### Diagnosis and reporting

Results are relayed via written correspondence and copied to participant and general practitioner. All biochemical measurements are performed in house at the University Hospitals of Leicester NHS trust. Glucose samples are taken in fluoride oxalate test tubes and placed immediately in a portable 4 litre 4°C refrigerator (also available on board the mobile screening unit). HbA1c% is analysed by a DCCT aligned Biorad Variant HPLC II system (Bio-Rad laboratories, Hemel Hempstead, UK). The imprecision coefficient of variation of this machinery is <0.1%, the reference intervals fit with national recommendations valid for carriers of variant Hb S, C and Q. Samples are processed within a maximum of two hours, using an Abbott Aeroset clinical chemistry analyser (Abbott laboratories, Maidenhead, UK), which employs the hexokinase enzymatic method. This machinery has an imprecision coefficient of variation of 1.61%. Serum total cholesterol, HDL-cholesterol, LDL-cholesterol and triglycerides are measured by means of enzymatic techniques (Dade Behring Dimension analyser, Newark, USA). Plasma creatinine is analysed with kinetic colorimetric methods. Plasma levels of urea and electrolytes, bilirubin, alanine aminotransferase, alkaline phosphatase and thyroid stimulating hormone are analysed by means of the Dade Behring Dimension analyser.

Participants are categorised according to World Health Organisation (WHO) criteria [33]. Diabetes is defined as a fasting blood glucose of greater or equal to 7 mmoll^-1 ^and/or 120-PG of greater than or equal to 11.1 mmoll^-1^. Impaired Fasting Glycaemia (IFG) is defined as a fasting blood glucose concentration of between 6.1 and 6.9 mmoll^-1 ^inclusive and IGT as a blood glucose concentration of between 7.8 and 11 mmoll^-1 ^inclusive. Impaired Glucose Regulation (IGR) is defined as any combination of IFG and/or IGT. The diagnosis of T2DM is confirmed by an in house physician on the basis of two abnormal glucose results obtained on separate visits, unless hyperosmolar symptoms suggestive of hyperglycaemia are reported at the screening visit. Asymptomatic individuals with a diabetes range OGTT are asked to maintain their current lifestyle and return for a confirmatory test (re screen) within one week. For a diagnosis of T2DM in asymptomatic individuals, one positive result from either a fasting and/or 120-PG is required on both visits. In the event of discordant OGTT results (eg. baseline diabetes followed by rescreen IGR) participants are categorised as having IGR (figure 2). Volunteers diagnosed with diabetes are entered into a cluster randomised controlled trial of multi-factorial cardiovascular risk intervention whilst those identified with IGR are given lifestyle advice and invited to join the ADDITION-Leicester prediabetes cohort study.

**Figure 2 F2:**
[figure not shown]
**ADDITION-Leicester algorithm for the diagnosis of pre-diabetes and screen-detected T2DM**.

### ADDITION-Leicester Pre diabetes cohort study

Non-diabetes range asymptomatic hyperglycaemia is of clinical relevance to screening programmes due to the associated increased risk of T2DM and cardiovascular disease. Volunteers found to be within fasting or post-challenge glucose categories of IFG and IGT (collective lay-term prediabetes) at baseline are provided with written lifestyle advice and invited for annual screening. The ADDITION-Leicester prediabetes cohort study annual screening protocol is identical to the baseline visit (table 1), all results are relayed to participant and general practitioner and those with diabetes range results are recalled for a second glucose tolerance test. The process for continued follow up differs however, as newly diagnosed T2DM is considered an endpoint and the case is returned to the care of the primary care specialist rather than entering the trial phase. Continued Prediabetes or normal glucose tolerance range results are invited for further annual assessments.

### Phase 2: A randomised controlled trial of multifactorial intervention in individuals with screen-detected T2DM

Phase 2 is a pragmatic, cluster randomised, parallel group trial among people with screen-detected T2DM comparing intensive multi-factorial treatment with routine care in general practice according to national guidelines.

Randomisation is performed by an independent committee provided with practice demographics, deprivation status and approximate T2DM prevalence of individual practices. Practices and not individuals are randomised via a minimisation procedure with a 1:1 ratio. The screen detected T2DM control group (routine care arm) receive "usual care" within the primary care setting, according to national recommendations for management of T2DM and cardiovascular disease [38]. These participants will be reviewed one and five years post diagnosis, when anthropometric and biochemical data will be collected. The screen detected T2DM intervention group (intensive care arm) are introduced to dedicated, specialist physicians and nurses who provide a structured, intensified, protocol-driven, multi-factorial approach again within the primary care setting (table 2).

**Table 2 T2:** ADDITION-Leicester algorithm for the management of hyperglycaemia, hypertension and dyslipidaemia.

	Basic Treatment TARGET	add if above TARGET	add if above TARGET +BMI>19 or creatinine>130	Supplementary treatment If still above TARGET	
Blood Glucose	***HbA1c <6.5%*** SMBG Tuition DESMOND Dietary Advice	***HbA1c >6.5%*** SMBG Tuition DESMOND Biguanide	***HbA1c >6.5%*** SMBG Tuition DESMOND Insulin	***HbA1c >6.5%*** Biguanide Sulphonylureas Thiazolidinediones THEN Stop TZD Add basal Insulin (bedtime)	***HbA1c >6.5%*** ***and on *** ***Biguanide*** ***Sulphonylureas*** ***Insulin*** (basal/bolus) Intensify & titrate Insulin

Blood Pressure	***BP *** ***< 130/80 mmHg*** No treatment	***BP *** ***>130/80 mmHg*** ACE	***BP >135/80 mmHg*** ARB CCB Thiazide	***BP *** ***>130/80 mmHg*** ACE ARB/CCB	Thiazide alpha/beta Blocker

Cholesterol	***<3.5 mmol/L*** Diet	**>*3.5 mmol/L*** ***TG >6.0 mmol/L*** Diet Statin Consider Ezetimibe/Fibrate			

Aspirin	75 mg to all patients, unless contraindications of gastrointestinal bleeding, ulcers or haemophilia. If Aspirin contraindicated, consider Clopidogrel.				

KEY

**ACE**: Perindopril 2-4 mg daily or Ramipril 2.5-10 mg daily

**SMBG**: self-monitored blood glucose

**Biguanide: **Metformin 1-2 g daily

**Sulphonylurea: **Gliclazide MR 30-120 mg daily or Glimepiride 1-4 mg daily

**Insulin: **Basal analogue: Glargine. Short-acting analogue: Novorapid or Premixed: Novomix30 twice daily

**Thiazolidinedione: **Pioglitazone 30-45 mg daily

**ARB: **Angiotensin receptor blocker: Losartan 25-50 mg daily

**CCB: **Calcium Channel Blocker: Amlodipine 5 mg daily

**Thiazide: **Bendrofluazide 2.5 mg daily

**Alpha/beta blocke**r: Doxazosin MR 4-8 mg or Bisoprolol 5-10 mg daily

**Statin: **Simvastatin 20-40 mg or Atorvastatin 20-40 mg daily

**Fibrate: **Fenofibrate (micro) 267 mg or Bezafibrate MR 400 mg daily

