#### Intensive care arm intervention

Care for the intensive arm is based upon a paradigm of multi-factorial intervention shown to improve mortality in T2DM [41]. Structured education (diabetes education and self-management for ongoing and newly diagnosed diabetes - DESMOND [42]) is initially offered to all patients in the intensive arm with attendance ideally, within the first two months of diagnosis. Sessions are delivered by two trained educators and aim to facilitate lifestyle changes in relation to dietary habits, physical activity levels, smoking cessation and glucose monitoring. Those participants who are unable, or decline the opportunity to attend the structured education programme are offered one-to-one advice with a dietitian. All volunteers are offered a glucometer, and encouraged to maintain a reflective diary. On-going professional support is provided in the first year through an individualised peripatetic clinic offering two monthly visits from a diabetes specialist nurse or physician. Ultimately, participants are encouraged to self-manage their diabetes by identifying personalised goals which facilitate individualised behaviour and lifestyle change.

Patients without specific contra-indications are advised to take aspirin 75 mg orally and prescribed lipid lowering therapy (simvastatin 40 mg once daily) if total cholesterol concentration exceeds 3.5 mmoll^-1^. An individualised, stepwise approach to management according to specified algorithms is adopted to ensure optimisation of hypertension, dyslipidaemia and hyperglycaemia according to protocol-driven targets using medication within existing licensed indications (table 2). Recommended drug choices take in to account treatment efficacy, side-effects and cost, the main priority being achievement of treatment targets whilst maintaining flexibility and low rates of adverse events. The approach is deliberately pragmatic with the final decision on choice of medication determined by the health care professional and patient. Treatment targets for the intensive care arm are based on complex interventions with proven efficacy in T2DM; HbA1c <7.0% with initiation of treatment at 6.5%, blood pressure <130/80 mmHg, and total cholesterol <3.5 mmoll^-1 ^[41]. After the first year, community visits are extended to every four months but continue to be guided by protocol driven blood pressure, HbA1c%, and lipid targets.

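### Table 2 reserves its insulin column for BMI >19 or creatinine >130, a condition most or nearly all patients above target meet, so as printed it does not mark out a subgroup for insulin instead of biguanide

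*Protocol article*

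**What the plan says.** The section on Phase 2 describes the intensive arm as structured and protocol-driven and refers to Table 2 for the algorithm. In the Blood Glucose row of that table:

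- The second treatment column applies to patients above target (HbA1c >6.5%) and gives "SMBG Tuition DESMOND Biguanide". The key identifies the biguanide as "Metformin 1-2 g daily".
- The third column carries the header "add if above TARGET +BMI>19 or creatinine>130", has the same HbA1c trigger, and gives "SMBG Tuition DESMOND Insulin".
- The first supplementary column, for patients still above target, reads "Biguanide Sulphonylureas Thiazolidinediones THEN Stop TZD Add basal Insulin (bedtime".

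The section on the intensive care arm intervention says that management follows the specified algorithms step by step, within licensed indications. It calls the approach pragmatic, with the "final decision on choice of medication determined by the health care professional and patient". The BMI condition is not restated or corrected anywhere else in the article.

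**The concern.** The second and third columns of the glucose row have the same trigger and the same background of self-monitoring tuition and structured education. Only the BMI and creatinine condition in the header separates them. If nearly everyone satisfies that condition, it cannot say who should have insulin in place of a biguanide.

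Table 2 defines the experimental treatment. Someone replicating or appraising the intensive arm needs to know which patients above target were meant to have insulin instead of metformin. Taken literally, the printed condition opens insulin at this early step to almost all of them.

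**Working it through.** The plan gives no figure for the share of patients meeting the condition, so there is nothing to reproduce. The check has two parts: how selective the condition is, and whether it fits the rest of the row.

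**1. Selectivity of the BMI clause.** BMI is in kg/m² (section on screening visit measurements), so the cut-off is 19 kg/m². The mean and SD are assumptions, because the article gives neither. With a normal distribution,

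P(BMI >19) = 1 − Φ((19 − mean)/SD).

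Two examples:
- Mean 26, SD 6: (19 − 26)/6 = −1.167, giving 0.878.
- Mean 32, SD 4: (19 − 32)/4 = −3.25, giving 0.9994.

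| Assumed mean | SD 4 | SD 5 | SD 6 |
|---|---|---|---|
| 26 | 0.960 | 0.919 | 0.878 |
| 28 | 0.988 | 0.964 | 0.933 |
| 30 | 0.997 | 0.986 | 0.967 |
| 32 | 0.9994 | 0.995 | 0.985 |

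A lower assumed mean of 25 with SD 6 still gives 84.1% (85.1% with a lognormal distribution). Because the clauses are joined by *or*, creatinine can only raise these shares.

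**2. What the creatinine clause does.** In an *or* condition, the second clause decides only for patients who fail the first. As printed, creatinine matters only for those with BMI of 19 or less, which is 1 − 0.878 = 12.2% down to 1 − 0.9994 = 0.06%. The clause is almost idle. With the sign reversed, BMI would select that same 12.2% to 0.06%, and creatinine would decide for everyone else, so both clauses would do work.

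**3. Fit with the rest of the glucose row.**
- The third column is not simply a further step on top of the second: its cell omits the biguanide.
- The supplementary column lists the biguanide again, with a sulphonylurea and a thiazolidinedione, then stops the thiazolidinedione and adds basal insulin. That cannot be the usual route if nearly every patient above target has already qualified for insulin.
- A column that replaces metformin with insulin and is tied to raised creatinine reads naturally as an exception for patients unsuited to metformin. A low BMI fits such an exception; a BMI above 19 does not.

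**4. Reading fault.** Both inequality signs appear correctly elsewhere in the same table (HbA1c and blood pressure targets on one side, triggers on the other), so a character flipped in extraction is unlikely.

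No patient count is attempted. The article does not give the size of the intensive arm or the share with HbA1c above 6.5%, and diagnosis is by glucose.

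**The case against.** Several points on the other side stand.

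- **The intended condition is not known.** A reader might infer that the sign is shown to be inverted. The article shows only that the printed condition barely discriminates; a wrong number would produce the same symptom. The header also stands over the blood pressure row, where BMI <19 gives no evident reason for the drugs listed. The inversion is the likeliest explanation of the glucose row, but it remains an inference.
- **An order is suggested.** A reader might infer that the table leaves it open which drug comes first. That goes too far: the biguanide column precedes the insulin column, the text describes a stepwise approach, and the supplementary column starts from a biguanide. This does not repair the condition, which still fails to say who is the exception.
- **Care is not bound by the misprint.** Specialist physicians and nurses deliver the treatment and share the final drug choice with the patient. Biguanide-first care also satisfies the second column. Nothing supports inferring that patients were wrongly started on insulin or that the primary comparison is affected.
- **The shares are assumed.** At the low end about one patient in eight fails the BMI clause, so *nearly all* fits the upper part of the range and *most* fits the lower.

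The same column also prints "BP >135/80 mmHg", whereas the text gives a target of "blood pressure <130/80 mmHg". A reader might take this for a second error. The document does not support that, because a threshold for escalating treatment may differ from a target.

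**Conclusion.** The point holds as a minor error in the specified intervention. As printed, the condition admits about 88% to 99.9% of patients under normal BMI with mean 26 to 32 and SD 4 to 6 kg/m². It therefore does not mark out a group for insulin instead of a biguanide, and it conflicts with the later step that reserves basal insulin until after oral triple therapy. The percentages rest wholly on assumed BMI distributions, but the conclusion holds across the range tried. That BMI <19 was intended is probable, not established. No sample size, power or analysis figure depends on this condition.

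**What to change.** Check the header of the third treatment column against the full algorithm and correct the threshold, probably to BMI <19 or creatinine >130. Add a phrase stating that in the glucose row this column is the alternative for patients unsuited to a biguanide. The cost is one corrected condition and one clarifying phrase in the table. Table 1 already schedules BMI and renal function at the trial visits, so no extra tests, visits or patients are needed.

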#### Routine care arm intervention

Screen-detected T2DM cases entering the control group (routine care arm) receive the standard of care normally provided by their primary health care team. Within 24 hours of diagnosis a letter detailing the results of screening is faxed to the practice, the participant is informed (where possible via telephone contact) and an urgent appointment with their general practitioner advised.

At the time of randomisation each practice is sent a copy of and electronic links to Leicestershire evidence based guidelines adapted from national recommendations for diabetes care http://www.leicestershirediabetes.org.uk/[38]. At the time of writing these included local targets and protocol considered appropriate for effective cardiovascular risk management in T2DM. Specific local recommendations advise a glycosylated haemoglobin (HbA1c%) of <7.0%, blood pressure of <140/85 mmHg and a serum total cholesterol of <4.0 mmoll^-1^. Systematic evidence-based standards of care are expected of all UK general practices engaged in delivering diabetes services as outlined in the NHS National Service Framework for Diabetes [39]. All participating practices are also performance managed by active participation in the quality outcomes framework for diabetes [40].

The routine care arm will be reviewed one and five years post diagnosis when only anthropometric and biochemical data will be collected. The intensive treatment team do not engage in the management of these patients and general practitioners are asked to follow usual referral procedure if specialist advice or intervention is required.

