#### Secondary and intermediate outcomes

Secondary outcomes of ADDITION-Leicester are a microvascular complication composite of diabetic retinopathy, neuropathy or microalbuminuria, a vascular atherosclerosis surrogate (carotid femoral pulse wave velocity), all cause mortality (assessed by participants tagging with the Office for National Statistics), non-fatal cardiovascular events, hospitalisation, health service cost and quality of life indicators.

Intermediate outcomes are measured annually in the intensive care arm and at one, three and five years in the routine care arm (table 1). These include HbA1c%, blood pressure, total cholesterol, microalbuminuria, self-reported hypoglycaemic episodes, weight, physical activity, ankle-brachial pressure indices and smoking status.

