### Statistical methods and power calculation

Assuming a prevalence of screen-detected diabetes of 4.5%, we calculated a target of 7,000 (30% (2,100) South Asians) volunteers over three years sufficient to identify a screen-detected T2DM cohort (n = 225) demonstrating a 6% difference (80% power, alpha 0.05) between routine and intensive groups at one year assuming an intra cluster correlation coefficient of 0.14 and allowing for a loss to follow-up of 15%.

The benefits of screening and intensive treatment will be assessed using an intention to treat and allowing for clustering of patients by practice. The UKPDS CHD score at 5 years will be compared along with all secondary outcomes by treatment group, adjusting for differences in baseline variables. Estimates will be presented with 95% confidence intervals to reflect uncertainty in estimations. Sensitivity analysis assuming a range of outcomes for non-completers will be informed by baseline data. The primary perspective for the cost analysis will be the health service, with personal costs as a secondary perspective. The costs of intensive intervention will be compared with unit change in health utility at one year. Costs at one year and future costs derived from existing data will be compared with modelled risk of death and cardiovascular events, with appropriate sensitivity analysis. The cost of screening and the screening plus intensive treatment will be compared with changes in health utility from questionnaire data.

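### The protocol contradicts itself on routine-arm follow-up: two visits limited to anthropometry and biochemistry in one place, three visits with a wider set of measures in another

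*Protocol article*

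**What the plan says.** Four places in the protocol article describe routine-arm follow-up.

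- **Phase 2 (trial description):** "These participants will be reviewed one and five years post diagnosis, when anthropometric and biochemical data will be collected".
- **Routine care arm intervention:** "The routine care arm will be reviewed one and five years post diagnosis when only anthropometric and biochemical data will be collected". This repeats the two visits and adds a restriction on content.
- **Secondary and intermediate outcomes:** intermediate outcomes are "measured annually in the intensive care arm and at one, three and five years in the routine care arm", with a reference to Table 1. The list reads: "These include HbA1c%, blood pressure, total cholesterol, microalbuminuria, self-reported hypoglycaemic episodes, weight, physical activity, ankle-brachial pressure indices and smoking status".
- **Table 1:** the year 1 and year 5 columns are headed for both arms. The year 3 column also includes the routine arm, with an asterisk on the word for the intensive arm. Years 2 and 4 are for the intensive arm.

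The secondary outcomes include "a microvascular complication composite of diabetic retinopathy, neuropathy or microalbuminuria" and quality of life. The section Statistical methods and power calculation compares the five-year risk score and all secondary outcomes by treatment group. For the economic analysis it adds: "The costs of intensive intervention will be compared with unit change in health utility at one year".

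**The concern.** The sentence in Routine care arm intervention is a rule about what to collect, and it appears in the section that a team responsible for control participants would consult. Taken literally, it excludes measures on which planned between-arm comparisons depend. A loss of that kind would be confined to one arm. It could not be repaired by imputing from baseline, because what would be missing is the control follow-up itself.

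The number of visits is also in conflict. With two control visits there is no year-three comparison of intermediate outcomes; with three there is.

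**Working it through.** No sample size or error rate enters this point, so the check is a comparison of the passages.

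**Visits.** Phase 2 and Routine care arm intervention give years 1 and 5, which is two visits. The outcomes section and Table 1 give years 1, 3 and 5, which is three.

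**Content.** Table 1 sorts its rows into classes, so the article's own classification can be used to decide what the restrictive sentence allows.

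| Measure | Class in Table 1 | Allowed by the restrictive sentence | Years 1 and 5, both arms | Year 3 |
|---|---|---|---|---|
| HbA1c, total cholesterol, urine albumin:creatinine ratio | Biochemical | Yes | Ticked | Ticked |
| Weight | Anthropometric | Yes | Ticked | Ticked |
| Blood pressure | Medical procedure | No | Ticked | Ticked |
| Foot check | Medical procedure | No | Ticked | Ticked, starred |
| Smoking | Interview questionnaire | No | Ticked | Ticked, starred |
| Physical activity (IPAQ) | Self-report | No | Ticked | Ticked, starred |
| EQ-5D | Self-report | No | Ticked | Ticked, starred |
| Michigan neuropathy | Self-report | No | Ticked | Ticked, starred |
| Hypoglycaemic episodes | No named row | No | – | – |
| Ankle-brachial index | No row of its own | No | – | – |
| Retinal examination | No row | No | – | – |

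**Intermediate outcomes.** Nine are named. The restrictive sentence allows four: HbA1c, total cholesterol, microalbuminuria and weight. It excludes 9 − 4 = 5: blood pressure, hypoglycaemic episodes, physical activity, ankle-brachial index and smoking.

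**Microvascular composite.** Of its three parts only microalbuminuria is biochemical, so 3 − 1 = 2 parts (retinopathy and neuropathy) would be unobserved in the routine arm. The composite would then be built from different components in the two arms.

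**Quality of life and utility.** EQ-5D and the diabetes-specific scales are questionnaires, so neither is allowed. One-year utility would exist for the intensive arm alone.

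**Retinal examination.** It is described only under Intensive care arm intervention, for annual visits V1 to V4. No routine-arm schedule is stated. The operators are said to be blinded to allocation, which suggests that both arms were intended, but the text does not say so.

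**Year three.** Table 1's key does not define the star in the year-3 column. If it means intensive arm only, as the column heading suggests, the routine arm has five of the nine intermediate outcomes at year 3: HbA1c, blood pressure, cholesterol, microalbuminuria and weight. Smoking and physical activity are starred, so Table 1 would then disagree with the outcomes section on those two. Hypoglycaemic episodes and ankle-brachial index have no row of their own, although the foot examination described for the intensive arm includes the index.

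**The case against.** The strongest reply is that the document as a whole does schedule most of these data. Table 1 is the detailed schedule. It ticks blood pressure, foot check, smoking, EQ-5D, physical activity and neuropathy for both arms at years 1 and 5, and the outcomes section expressly has the intermediate outcomes measured in the routine arm. The restrictive sentence sits next to a statement that the intensive team does not manage these patients, so it may be loose shorthand for measurement without treatment. Phase 2 makes the same statement without the limiting word.

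Most of this stands, and it rules out two stronger readings that a reader might infer.

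- **That control-arm follow-up is entirely missing for everything except laboratory results.** This follows only if one sentence overrides Table 1 and the outcomes section. Even then it fails for weight, which is anthropometric, and for all-cause mortality, which comes from national statistics tagging and not from visits.
- **That the primary contrast is biased.** The article does not list the inputs of the UKPDS equation, Table 1 schedules blood pressure and smoking for both arms at year 5, and nothing says that control-arm inputs would be carried forward or imputed.

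The reply does not remove the contradiction. The limiting word is explicit, the visit counts differ whatever reading is taken of the content, and Table 1 cannot settle the retinal examination because it has no row for it. A condensed article may leave that schedule to the full protocol, so the retinal gap is a gap in this text and not proof of one in the trial.

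**Conclusion.** The point holds as an internal contradiction: two routine-arm visits against three, and a restriction on content against a table and outcome list that require more.

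The consequence is conditional. If the restrictive sentence were followed, the routine arm would lack visit data for five of nine intermediate outcomes, two of three parts of the microvascular composite, quality of life and one-year utility. These counts rest on Table 1's own classes. If Table 1 is followed, most of that loss does not arise, and three matters remain open: the retinal schedule in the routine arm, the meaning of the star, and year-three smoking and physical activity.

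No effect on the primary coronary risk score is claimed. It would need an assumption about the equation's inputs that this article does not supply.

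**What to change.** 1. In Routine care arm intervention, delete the clause that limits collection to anthropometric and biochemical data.
2. State the same routine-arm visits in Phase 2, Routine care arm intervention, Secondary and intermediate outcomes, and Table 1.
3. Give one visit-by-measure list per arm that covers every outcome compared between arms.
4. In that list, define the Table 1 star. Then reconcile year-three smoking and physical activity with the outcomes section, either by scheduling them for the routine arm or by amending that section. Simply giving the routine arm the un-starred items would leave this conflict in place.
5. Add rows for the retinal examination and the ankle-brachial index, showing the visits at which both arms are assessed.

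The cost is mainly wording, since Table 1 already has most of these measures in both arms at years 1 and 5. The possible exceptions are the retinal examination and any year-three measures newly confirmed for the routine arm. The article reports that screening is complete and that the intervention ran in tandem with it, so some follow-up visits may already have taken place. For those, the sponsor should record what was actually collected in each arm.
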